### 2.8. Primary Outcomes

#### 2.8.1. ANEMIA Package

This set captures anemia-related biomarkers and systemic effects, including: (1) EPO and HIF-1α (for assessing erythropoiesis and hypoxia response); (2) 5-diff blood morphology (to provide a detailed blood profile); (3) creatinine + eGFR (kidney function markers for a comprehensive evaluation of metabolic status); (3) ALT + AST (liver function markers for a comprehensive evaluation of metabolic status); (5) glucose and insulin (metabolic and glycemic control); (6) lipid panel (overall lipid profile related to systemic health); (7) iron metabolism (TIBC, Iron, Ferritin) and B12 (to evaluate iron stores and deficiency-related anemia); and (8) albumin and CRP (markers of inflammation and nutritional status). In addition to EPO and HIF-1α, we will measure reticulocyte count as a direct indicator of bone marrow response to assess dynamic changes in erythropoiesis.

#### 2.8.2. STRESS Package

This set captures markers related to oxidative stress, hormonal response, and physiological load, including: (1) ROS (measures reactive oxygen species levels); (2) cortisol, GABA, Dopamine, and Serotonin (stress hormones and neurotransmitters); (3) allostatic load (CRP, fibrinogen, HbA1c, DHEA-S, blood pressure (SBP, DBP), and heart rate (HR), to assess chronic stress burden); and (4) anthropometry (BMI, BSA, and WHR, reflecting body composition and risk).

#### 2.8.3. IMMUNO and GENETICS Packages

We will analyze a comprehensive cytokine panel (24-plex or 45-plex) to capture the full spectrum of immune modulation in CRC patients. This panel includes pro-inflammatory (e.g., TNF-α, IL-1β, IL-6), anti-inflammatory (e.g., IL-10), chemotactic (e.g., MCP-1, MIP-1α/β), and growth factors (e.g., VEGF, PDGF) that are collectively relevant for tumor progression, immune cell recruitment, and therapy response in CRC. Multiplex immunoassay technology (e.g., Luminex or similar platforms) will be employed to simultaneously measure these cytokines in a single sample, which enhances throughput, reduces sample volume requirements, and minimizes technical variability compared with individual ELISAs.

### 2.9. Secondary Outcomes

#### 2.9.1. Perceived Stress Questionnaire (PSQ)

The PSQ is dedicated to measuring different dimensions of stress responses. Consisting of 30 items, the PSQ was developed as an instrument for assessing stressful life events and circumstances that tend to trigger or exacerbate disease symptoms. The scale is specifically recommended for clinical settings, though it has been employed in research studies as well. A psychometric evaluation of the scale found internal consistency values ranging from 0.90 to 0.92 and a test–retest reliability of 0.82. In order to complete the PSQ, respondents receive one of two sets of scoring instructions. The general questionnaire queries stressful feelings and experiences over the course of the previous year or two, while the recent questionnaire concerns stress during the last month. Respondents indicate on a scale from 1 (“almost never”) to 4 (“usually”) how frequently they experience certain stress-related feelings. Higher scores indicate greater levels of stress. A total score is found by tallying each item (questions 1, 7, 10, 13, 17, 21, 25, and 29 are positive and are scored according to the directions accompanying the scale). A PSQ index can be found by subtracting 30 from the raw score and dividing the result by 90, yielding a score between 0 and 1 [38].

#### 2.9.2. Hospital Anxiety and Depression Scale (HADS)

The HADS will be used to capture patient perceptions of mental health. It is a widely used screening tool designed to assess anxiety and depression levels in medical patients. Comprising 14 items, it is divided into two subscales: 7 items measure anxiety (HADS-A) and 7 items measure depression (HADS-D). The responses are scored on a 4-point Likert scale, where higher scores indicate greater levels of anxiety or depression. Importantly, the HADS was developed to avoid the confounding effects of physical illness on mood assessments, making it especially suitable for patients in hospital or clinical settings. The total scores for each subscale range from 0 to 21, with thresholds indicating mild, moderate, or severe anxiety or depression. The HADS is extensively used in research and clinical practice, particularly for evaluating psychological well-being in patients with chronic diseases, such as cancer or cardiovascular conditions, as well as during therapeutic interventions like NBO therapy. Its simplicity, reliability, and focus on emotional health make it an effective tool for identifying mental health issues in medically ill patients [39].

#### 2.9.3. EuroQol-5 Dimension (EQ-5D)

The EQ-5D will be used to assess health-related quality of life across five key domains. Each domain reflects a distinct aspect of health, making the EQ-5D a comprehensive measure for tracking changes in overall health and well-being. The EQ-5D contains five domains, each with one question. Mobility measures a patient’s ability to move around. The question may ask, “Are you able to walk about?” Responses range from no problems in walking to being confined to bed. Self-care assesses whether the patient can manage basic personal needs, such as washing and dressing. Responses indicate whether they have no problems, slight problems, moderate problems, severe problems, or are unable to wash or dress. The ‘usual activities’ domain evaluates the patient’s ability to perform everyday activities, including work, study, housework, and leisure activities. Patients indicate if they have no issues, slight problems, moderate issues, severe issues, or extreme difficulties performing these activities. Pain/discomfort assesses the intensity of pain or discomfort the patient is currently experiencing. Responses range from no pain or discomfort to extreme pain or discomfort. Anxiety/depression measures the patient’s level of anxiety or depression, with options from no anxiety/depression to extreme anxiety/depression. Each domain is rated on a scale of 1 to 3 or 1 to 5, depending on the version (EQ-5D-3L or EQ-5D-5L). The scores from each domain are combined into a five-digit number that represents the patient’s health state. Health states can be converted into a single index score using country-specific value sets, which allow researchers to calculate a weighted score for the health state. This index score is often used in economic evaluations of healthcare interventions, like calculating Quality-Adjusted Life Years (QALYs) [40].

### 2.10. Statistical Analysis

Descriptive statistics will be used to summarize study results. Central tendency and dispersion measures will be calculated using parametric or non-parametric methods depending on data distributions. Repeated measures data (V1, V2, V3, V4, and V5) will include ordinal and interval data analyzed with repeated measures ANOVA (parametric) or the Friedman test (non-parametric). Data normality will be verified with the Shapiro–Wilk test. Depending on the distribution, data will be presented as means with standard deviations (parametric) or medians with interquartile ranges (IQRs) (non-parametric). Comparisons between baseline (V1) and follow-up (V4, V5) visits will use the Wilcoxon signed-rank test for paired variables and the Friedman test for multiple comparisons. Post hoc analysis (for significant Friedman tests) will apply Wilcoxon tests with Bonferroni corrections. For between-group comparisons (intervention vs. control), the Mann–Whitney U test will be used.

A comprehensive sample size analysis was conducted to ensure that the study is adequately powered to detect a statistically significant effect of NBO therapy on erythropoiesis stimulation among patients undergoing chemotherapy. The primary endpoint considered was the assumed 40% difference between the active NBO group and the placebo group in the primary outcome measure related to erythropoiesis, such as erythropoietin (EPO) levels. To achieve adequate statistical power, the analysis aimed for 80% power (β = 0.20), indicating a high probability of detecting a true effect if it exists, at a significance level of 5% (α = 0.05), which is the conventional threshold for statistical significance. Effect size estimation was based on Cohen’s (1992) [41] classification, where a small effect size ranges from 0.1 to 0.29, a medium effect size ranges from 0.3 to 0.49, and a large effect size ranges from 0.5 to 1. An effect size corresponding to a medium to large effect was anticipated due to the expected impact of NBO on erythropoiesis.

For the CRC groups (Groups 1 and 2), it was determined that 127 patients per group are required. This accounts for a potential 30% dropout rate, ensuring that the final sample maintains the desired power and accounting for the challenges associated with patient retention over the study period. The sample size calculations were performed using G*Power software (version 3.1.9.7 or the latest version). The parameters used in the calculation included the expected effect size (d), calculated based on the anticipated difference and standard deviation from pilot studies or the existing literature. An allocation ratio (N2/N1) of 1 was used, indicating equal allocation between the active NBO and placebo groups. The test family selected was *t*-tests for means between two independent groups, focusing on the difference between two independent means.

Assumptions made during the calculation included a confidence level of 95% and the use of a two-tailed test, considering the possibility of the effect in both directions. It was also assumed that the variability in outcome measures would be similar across groups, which is important for the validity of the statistical tests used.

The rationale for this sample size is to ensure that the study is sufficiently powered to detect clinically meaningful differences between the active NBO and placebo groups in the primary outcome measures. By accounting for a 30% dropout rate, the study design acknowledges the realities of clinical research involving patients undergoing chemotherapy, who may experience side effects or other factors leading to withdrawal from the study.

An interim analysis will be conducted after 50% of participants have completed the study. The research team will assess data on safety and efficacy trends during this analysis. Based on interim findings, sample size adjustments may be considered, adhering to statistical guidelines to control for Type I error inflation and ensuring the integrity of the study.

Statistical analyses will be performed using software such as SPSS (version 26 or later) and R (version 4.0 or later) with appropriate packages. Supplemental tools like SAS 9.4 M8 or Stata 19 may be used if needed. Data management will involve entering data into a secure database with validation checks to ensure accuracy. Data cleaning procedures will be implemented prior to analysis to address any inconsistencies or errors.

Handling of missing data is an important aspect of the analysis plan. An intention-to-treat (ITT) analysis will be conducted, including all randomized patients in the analysis according to their assigned groups. Missing data will be handled using appropriate statistical methods such as multiple imputation or last observation carried forward (LOCF), depending on the nature and extent of the missing data. Additionally, a per-protocol (PP) analysis will be conducted as a secondary analysis, including only patients who completed the study without major protocol deviations, to assess the robustness of the findings.

Adjustment for multiple comparisons will involve the use of Bonferroni correction or other suitable methods when conducting multiple statistical tests. This approach helps control the overall Type I error rate, reducing the likelihood of false-positive findings due to multiple tests. Sensitivity analyses will also be performed to assess the robustness of the results under different assumptions and statistical models, providing additional confidence in the study conclusions.

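### A Shapiro–Wilk check picks the longitudinal test and the reported summary from the trial's own data, and a marker that fails it loses the only named longitudinal analysis able to compare change over visits between arms

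*Protocol article*

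**What the plan says.** All the relevant statements are in the first paragraph of section 2.10 of the protocol article.

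- Longitudinal test: data from V1 to V5 are to be "analyzed with repeated measures ANOVA (parametric) or the Friedman test (non-parametric). Data normality will be verified with the Shapiro–Wilk test".
- Summary measure: "Depending on the distribution, data will be presented as means with standard deviations (parametric) or medians with interquartile ranges (IQRs) (non-parametric").
- Between-arm test, with no normality condition: "For between-group comparisons (intervention vs. control), the Mann–Whitney U test will be used".
- Baseline versus follow-up, also with no condition: "Comparisons between baseline (V1) and follow-up (V4, V5) visits will use the Wilcoxon signed-rank test for paired variables".

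The article does not give the level of the Shapiro–Wilk test. It does not say whether the test is run per marker, per visit, per arm or on residuals, or what happens when verdicts conflict. Section 3 (Results) describes the primary outcomes as changes in EPO, oxidative stress and immune markers, with values before and after the intervention compared between active and placebo NBO.

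**The concern.** A preliminary normality test is being used as a selector. It does not merely choose between two ways of testing one hypothesis. One branch concerns means and can ask whether the course over visits differs by arm. The other concerns within-patient ranks and cannot ask that. Section 3 poses a question about change between arms, so the choice matters for the longitudinal analysis of each marker, and it is settled only once the data are in.

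The same applies to reporting. One marker may appear as mean and SD and the next as median and IQR, for no reason beyond the outcome of a test that depends strongly on sample size. If verdicts are taken by visit or arm, a single marker could be shown on two scales, and its change or its difference between arms could not be read directly from the table.

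**Working it through.** The article prints no figure for this point, so there is none to reproduce. The check has two parts: what the selector controls, and how stable its verdict would be.

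**1. What the selector controls**

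| Analysis in section 2.10 | Chosen by distribution? | Can compare arms? |
|---|---|---|
| Repeated-measures ANOVA, V1–V5 | Yes | Yes, if arm and arm-by-visit are included |
| Friedman, V1–V5 | Yes | No |
| Mean/SD or median/IQR | Yes | Descriptive |
| Mann–Whitney U, intervention vs control | No | Yes |
| Wilcoxon signed-rank, V1 vs V4/V5 | No | No |

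**2. Why Friedman cannot carry the arm.** Each patient's five values are replaced by the ranks 1 to 5. The rank sum is 1 + 2 + 3 + 4 + 5 = 15 and the mean rank is 15/5 = 3 for every patient in either arm, so any difference in level between arms disappears. A difference in pattern between arms is not tested either. On pooled data the test asks only whether visits differ overall. Run in each arm separately, it gives two p-values but no test of their difference.

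**3. How stable the verdict is, if taken by visit and arm**

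Inputs from section 2.10: five visits and two arms, hence 5 × 2 = 10 cells per marker; 127 patients per arm; 30% dropout, hence 127 × 0.7 = 88.9, about 89. Assumptions: Shapiro–Wilk at 0.05 (the trial's general level; none is given for this test), correlation 0.6 between visits, and the distributions below. The article gives no SDs or coefficients of variation (CVs). There were 1,000 simulated data sets per setting.

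Let q be the probability that one cell is declared non-normal. If cells were independent, the probability that the ten verdicts are not all the same would be 1 − (1 − q)^10 − q^10. For exactly normal data at n = 89, q = 0.050 and this is 1 − 0.95^10 = 1 − 0.599 = 40.1%.

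| Assumed marker | n per arm | q | Ten verdicts disagree, simulated | Independence formula |
|---|---|---|---|---|
| Normal | 89 | 5.0% | 37.9% | 40.1% |
| Normal | 127 | 4.8% | 36.9% | 38.9% |
| Log-normal, log-SD 0.2 | 89 | 50.5% | 99.1% | 99.8% |
| Log-normal, log-SD 0.2 | 127 | 66.0% | 96.2% | 98.4% |
| Log-normal, log-SD 0.3 | 89 | 83.4% | 79.1% | 83.7% |
| Log-normal, log-SD 0.3 | 127 | 94.3% | 41.0% | 44.4% |
| Log-normal, log-SD 0.5 | 89 | 99.7% | 3.2% | 3.0% |
| Log-normal, log-SD 0.5 | 127 | 100.0% (rounded) | 0.2% | 0.0% |
| Log-normal, log-SD 0.8 | both | 100.0% | 0.0% | 0.0% |

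Simulation error near 37% is about 1.96 × √(0.37 × 0.63/1000) = 3 percentage points. A separate run at 100 per arm gave 39.7% (normal), 98.6% (CV 20%) and 73.3% (CV 30%). With log-SD = √ln(1 + CV²), those CVs are log-SDs of 0.198 and 0.294, so the runs agree. An assumed bounded integer score (6 + 4z, rounded, limited to 0–21) gave disagreement of 80.6% at n = 89 and 11.9% at n = 127. Over all settings, the two arms disagreed at one given visit in 0% to 51% of runs.

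**4. Reading the result.** Under strong skew the verdict is stable, and it consistently sends the marker to Friedman. Under mild skew verdicts conflict and no rule resolves them. Under exact normality, at least one cell fails by chance in more than a third of cases.

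**The case against.** The strongest reply is that the randomized comparison does not depend on the check. Mann–Whitney U is fixed for intervention versus control, and Wilcoxon for V1 versus V4/V5. That stands in full. A reader might infer that Shapiro–Wilk decides the treatment-effect test, or that skewed markers cannot be compared between arms at all. The text supports neither: every marker gets the Mann–Whitney comparison. What is lost is the longitudinal comparison. Mann–Whitney takes one visit or one change score at a time, and the article does not say whether it will be applied to change or at which visit.

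A reader might also infer that scales will usually differ between visits and arms. That is not supported. It presumes ten separate tests, which the article does not state, and disagreement then runs from about 0% to 99% depending on skew. ANOVA or Friedman over V1–V5 also needs one choice across visits, so a split by visit can affect only the summaries. A split by arm could reach the test only if arms were analysed separately.

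Section 2.5 keeps all but the NBO operators blinded until the analysis is complete, and those operators take no part in it. This limits deliberate selection but does not fix the hypothesis. Section 2.10 promises sensitivity analyses under other models, without saying which analysis leads. Nothing here shows an inflated Type I error, bias or a changed conclusion. Finally, an article may leave detail to an analysis plan, but this rule is stated, so it can be judged as stated.

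**Conclusion.** The point holds in a limited form. A data-driven normality check selects the V1–V5 test and the reported summary, and its two branches test different hypotheses. A marker that fails loses the only named longitudinal method that could test the difference in change between arms that section 3 describes. This assumes that the ANOVA branch would include arm and arm-by-visit, which the article does not spell out.

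The reported scale can change between markers. Within one marker it may change if testing is by visit or arm: about 37–40% of cases for normal data, 96–99% at log-SD 0.2, and close to 0% from log-SD 0.5 upward. These figures rest on the assumed distributions, correlation and test level, and they count split verdicts rather than errors in inference. Severity is minor to moderate, because the fixed between-arm and baseline-to-follow-up tests are untouched.

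**What to change.** Remove Shapiro–Wilk as a selector and state instead:

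- **Scale, fixed by type of variable.** Concentration markers (EPO, cytokines, CRP, ferritin, cortisol and similar) on the log scale, with geometric means and ratios. Questionnaire scores and vital signs on the raw scale, with means. Use the same scale and summary in both arms and at all visits.
- **One longitudinal between-arm analysis, named in advance for every variable**, for example a linear model for repeated measures with arm, visit and arm-by-visit.
- **Residuals checked by plot**, without a test that switches the analysis.
- **Mann–Whitney U kept as a rank-based sensitivity analysis**, reported whatever the distribution looks like. The text should say openly that it moves from main to supporting analysis, since it is now the fixed between-arm test.

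The cost is a few sentences and slightly more reporting. A few markers may fit the preset scale less well, which the rank-based analysis covers. No visit, procedure or stated sample size changes, and section 3 schedules the first enrolment for March 2026.

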### 2.5. Randomization and Blinding

Participants will be randomized in a 1:1 ratio to the active NBO (study) or placebo NBO (control) group using a stratified randomization method. Stratification factors include CRC stage (II vs. III vs. IV) and baseline hemoglobin levels (<12 g/dL vs. ≥12 g/dL), as these variables can significantly influence treatment outcomes and the incidence of anemia. A computer-generated allocation sequence will be used within each stratum to ensure an even distribution of these characteristics across the two study arms. Only the NBO operators (who are not involved in data collection or analysis) will have access to the allocation list to administer the assigned intervention. All other study personnel and participants will remain blinded to group assignments.

Patients and clinical staff (excluding NBO operators who administer the therapy) will be blinded to the treatment allocations. Placebo NBO sessions mimic active NBO conditions without therapeutic oxygen adjustments. Both patients and clinical staff involved in patient care and data collection will be blinded to the treatment allocations. NBO operators who administer the therapy will not be blinded in order to ensure the correct delivery of the intervention. They will be trained to maintain confidentiality and avoid any disclosures that could compromise blinding. Both active NBO and placebo NBO sessions will be conducted in chambers that are identical in appearance and setup. This includes similar equipment, procedures, and environmental conditions in order to prevent patients and blinded staff from discerning group assignments.

Unblinding will occur after the database is locked and completion of statistical analysis. Immediate unblinding is permissible in medical emergencies where treatment knowledge is essential for patient care. Unblinding may occur immediately if a serious adverse event or medical emergency arises where knowledge of the treatment allocation is essential for the patient’s safe and effective management. The decision to unblind in an emergency will be made by the principal investigator or a designated medical officer.

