## 3. Results

The results of this study will focus on primary outcomes, including changes in erythropoietin (EPO) levels, oxidative stress markers, and immune function parameters, comparing pre- and post-intervention values between the active NBO and placebo NBO groups. Secondary outcomes will assess improvements in patient-reported outcome measures (PROMs), stress reduction, and psychological well-being based on standardized assessment tools, including the Perceived Stress Questionnaire (PSQ), Hospital Anxiety and Depression Scale (HADS), and EuroQol-5D (EQ-5D).

We anticipate that participants in the active NBO group will exhibit greater erythropoiesis stimulation, lower inflammatory cytokine levels, and improved stress adaptation compared with the placebo group. Furthermore, this study may provide insights into the long-term benefits of NBO therapy by analyzing patient outcomes at 3- and 6-months post-intervention.

Patient recruitment in the clinical setting is expected to be completed by 2030. Screening for eligible participants, based on the predefined inclusion and exclusion criteria, will be finalized in 2028. Informed consent will be obtained from all eligible study participants before enrollment, with the first participant scheduled to be enrolled in March 2026. Data analysis is projected to begin in June 2030, followed by the publication of primary and final results.

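### The only named between-arm test is a Mann–Whitney U test, which cannot adjust for baseline or the stratification factors and has no stated visit or outcome form: valid, but inefficient and under-specified

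*Protocol article*

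**What the plan says.** Section 2.10 of the protocol article names three groups of tests.

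- **Across visits.** Data from V1 to V5 are to be "analyzed with repeated measures ANOVA (parametric) or the Friedman test (non-parametric"), with Shapiro–Wilk as the normality check. No arm term and no arm-by-visit term is stated. A significant Friedman test leads to Bonferroni-corrected Wilcoxon tests.
- **Against baseline.** "Comparisons between baseline (V1) and follow-up (V4, V5) visits will use the Wilcoxon signed-rank test". V3 is not in this list.
- **Between arms.** "For between-group comparisons (intervention vs. control), the Mann–Whitney U test will be used". No visit, outcome form or covariate is given.

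Three other places bear on the point.

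- Section 2.5: "Stratification factors include CRC stage (II vs. III vs. IV) and baseline hemoglobin levels", cut at 12 g/dL. The section justifies both factors by their influence on outcome and on anemia. Neither appears anywhere in section 2.10.
- Section 2.7: V3 closes the intervention and carries the final round of primary and secondary assessments. V4 and V5 are the follow-up visits.
- Section 3: the results will focus on "comparing pre- and post-intervention values between the active NBO and placebo NBO groups".

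**The concern.** The trial randomises in order to compare arms, yet most of the named tests compare a patient with himself or herself over time. Every patient receives chemotherapy, so EPO, blood counts and cytokines may move in both arms for reasons unrelated to oxygen. Within-patient tests cannot separate that movement from a treatment effect.

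The one test that does compare arms leaves useful information aside. The V1 value is measured in everyone before the first session, and stage and haemoglobin stratum are recorded at randomisation. If these predict the outcome, adjusting for them narrows the confidence interval at no cost in patients. An unstratified test after stratified randomisation tends to be conservative when the strata are prognostic.

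Because neither visit nor outcome form is fixed, the same sentence in section 2.10 covers several different primary results: value or change, at V2, V3, V4 or V5. The test also yields a p-value without an estimate of how far the arms differ.

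**Working it through.** **Inputs from the documents (section 2.10).** "at a significance level of 5% (α = 0.05"); "the use of a two-tailed test, considering the possibility of the effect in both directions"; "the analysis aimed for 80% power (β = 0.20"); 1:1 allocation; two-sample t-test; 127 per group including 30% dropout.

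**Inputs not in the documents.** The standardised effect d, the SD, and the correlation r between the V1 value and the outcome. I back-solve d and take r from 0.3 to 0.7. Data are assumed normal.

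**Step 1: the plan's own figure.** Without d or an SD, 127 cannot be strictly reproduced. Working backwards:

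- Completers per arm: 127 × 0.7 = 88.9, so about 89.
- The d that gives 80% power with 89 per arm (two-sided t-test, α = 0.05) is 0.422. Going forward again, 89 / 0.7 = 127.1, which rounds up to 128, so this is close to the stated 127.
- Reading the 40% difference as d = 0.40 needs 100 completers, hence 100 / 0.7 ≈ 143, or 100 × 1.3 = 130. At 89 per arm that effect has 75.6% power by t-test.

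**Step 2: Mann–Whitney on visit values.** With normal data its efficiency relative to the t-test is 3/π ≈ 0.955, so 89 patients act like 89 × 0.955 ≈ 85. Power at d = 0.422 is about 78%. A simulation (4,000 runs per setting, d = 0.425) gives 78–79% whatever r is. Moving from the t-test to the rank test therefore costs about 2 points.

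**Step 3: baseline adjustment.** ANCOVA multiplies the residual variance by 1 − r², so the effective effect is d / √(1 − r²).

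| r | 1 − r² | 0.422 / √(1 − r²) | Power, ANCOVA | Mann–Whitney, values | Mann–Whitney, change from V1 |
|---|---|---|---|---|---|
| 0.3 | 0.91 | 0.443 | 84% | 78–79% | 63% |
| 0.5 | 0.75 | 0.488 | 90% | 78–79% | 78% |
| 0.7 | 0.51 | 0.591 | 97.5% | 78–79% | 94% |

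The two Mann–Whitney columns are simulated at d = 0.425. The same simulations put ANCOVA at 83%, 90% and 98%, in agreement with the formula. At r = 0.5 the adjustment is worth 89 / 0.75 ≈ 119 patients per arm instead of 89. Any gain from the two strata is additional and is not quantified, because the documents give no figure for their prognostic strength.

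**Step 4: validity.** With no treatment effect, all three tests rejected in 4.4–5.8% of simulated trials, in line with the nominal 5%.

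**Step 5: within-arm tests, if they were read as evidence of effect.** Suppose both arms change equally by 0.2 SD of the paired difference, with 89 per arm. Each arm's paired t-test is then significant with probability p = 0.463. Active significant and placebo not: p(1 − p) = 0.463 × 0.537 ≈ 0.25. Exactly one arm significant: 2 × 0.249 ≈ 0.50, falling to 0.17 if the common change is 0.35 SD.

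**The case against.** Much can fairly be said for the plan, and several stronger readings should be set aside.

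- **That the trial will infer benefit from significance in one arm only.** A reader might infer this from the weight given to paired tests. No section proposes it: section 2.10 names a separate between-arm test, and section 3 speaks of a comparison between arms. The 25% figure is a risk only if within-arm results were so used.
- **That baseline is ignored.** Not established. Section 3 leaves open that changes from V1 are compared, and those would use the V1 value. This objection stands, but it does not rescue efficiency: Mann–Whitney on change stays below ANCOVA at every r shown, and at r = 0.3 it does worse than on raw values.
- **That V3 is left out of the analysis.** It is not. V3 is in the V1–V5 set and can be reached through the conditional post hoc tests. It is missing only from the named paired contrasts with V1, in a sentence about follow-up visits.
- **That complete-case methods contradict intention-to-treat.** Section 2.10 offers multiple imputation or LOCF, either of which can complete the data, so there is no flat conflict.
- **That the Shapiro–Wilk check makes the between-arm test data-dependent.** It governs the choice between repeated-measures ANOVA and Friedman, and the summaries. The Mann–Whitney sentence carries no condition.
- **That model terms belong in a statistical analysis plan.** Often true, and the repeated-measures ANOVA could carry an arm-by-visit term. But section 2.10 does not merely stay silent here: it assigns between-group comparisons to a test that admits no covariates. The promised sensitivity analyses under other models are unnamed and do not supply a primary analysis.

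**Conclusion.** The point holds as one of efficiency and specification. The only between-arm test named cannot adjust for the V1 value or for the factors on which randomisation is stratified, and its visit and outcome form are open. The test is valid, and at the back-solved effect its power on visit values is about 78–79%, close to the planned 80%. What is given up is roughly 5 points of power at r = 0.3, 11 at r = 0.5 and 19 at r = 0.7, plus an estimate with a confidence interval.

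These sizes rest on normal data, 89 completers per arm, d of about 0.42 and an assumed r, none of which the documents state. The direction does not depend on the exact values: with normal data and any non-zero correlation, adjustment gains precision. This should be fixed, but it does not threaten the validity of the trial.

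**What to change.** Reword section 2.10 to name one primary between-arm analysis:

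- An ANCOVA, or a mixed model for repeated measures over V2–V5, of EPO (on the log scale if skewed), adjusted for the V1 value, CRC stage and haemoglobin stratum.
- The arm contrast at one stated visit, reported as an estimate with 95% CI. V3 fits section 2.7, where it closes the intervention, and the pre/post comparison in section 3.
- Friedman and Wilcoxon signed-rank tests within arms kept as description only, which also removes the need for the Shapiro–Wilk choice between repeated-measures ANOVA and Friedman.
- A rank test stratified by the randomisation factors (van Elteren) as sensitivity analysis.
- The sample-size paragraph aligned with the analysis chosen.

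Cost: rewording, slightly more analysis work and reliance on a model, which the rank-based sensitivity analysis guards against. No new patients, visits or measurements are needed. Section 3 schedules the first enrolment for March 2026, so the change can be made before any outcome data exist.
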